## Abstract

**Background:**

Currently, a conclusive experience on the uniform implementation and benefits of day hospice structures and interventions is lacking in Germany. The following questions should be clarified: (1) Which structural conditions and interventional measures should be established in day hospices from the point of view of patients, relatives, and specialist staff?; (2) Are the planned structures or interventions feasible and implementable under real conditions and accepted by patients, relatives, and staff?; (3) How can a final implementation and intervention catalog for day hospices be designed?; (4) Is this final catalog of services feasible, reasonable, economical, and effective under everyday conditions in day hospices?

**Methods:**

We planned to perform a multistage investigation, guided by the Medical Research Council Framework for the development and evaluation of complex interventions. In Stage 1, an initial theoretical construct on structures and interventions will be established through an extensive literature and guideline review on day hospices and through qualitative interviews. In a nominal group process, we will create a catalog of offers. In Stage 2, feasibility testing is conducted in a single-day hospice under real-life conditions using quantitative quality indicators and qualitative interviews. Structures and interventions can be adapted here if necessary. In a second nominal group process, a final structure and offer catalog is created, which is then implemented in Stage 3 in the day hospice under investigation and evaluated under real daily conditions through a process and effectiveness test. For this purpose, qualitative and quantitative quality indicators will be used and a comparative cohort of patients who are not cared for in the day hospice – but in the same network structure (oncology–palliative care network Lower Bavaria) – is examined.

**Discussion:**

Finally, the initial statements on the reasonable and realizable structures or interventions in day hospices and their benefits in daily real-life conditions as well as possible optimization processes shall be made.

**Trial registration:**

The study was retrospectively registered in the German Clinical Trials Register (DRKS-ID DRKS00031613, registration date April 04, 2023) and the display portal of the Center for Clinical Trials of the University Hospital Regensburg (Z-2022-1734-6, registration date July 01, 2023).

## Background

Day hospices, as another form of outpatient specialist palliative care, is aimed at, among other things, promoting “independence and (…) quality of life of people with a life-limiting illness, primarily through social interaction (group offerings, artistic offerings, café, and so on), rehabilitation, physiotherapy, occupational therapy, artistic therapies (art therapy, music therapy, etc.), and/or medical care for symptom control” [1]. Another focus of day hospices is respite care. The hourly or daily care of palliative patients by a day hospice allows family caregivers to meet their own needs and stabilizes the family environment, thereby ensuring care of family members at home [2–4].

Previous studies have shown a heterogeneous picture of the study methodology and day hospice structure and effects [1]. Several reviews have also shown evidence of high patient satisfaction in day hospices [2, 5], primarily due to social support experienced, restful environment offered by a day hospice, and opportunities for social interaction. Although various quantitative surveys did not demonstrate a global improvement in quality of life, attendance at a day hospice led to lower symptom burden and higher level of emotional well-being in sub-aspects [6, 7]. In sum, the limited (quantitative) evidence in the literature does not yet provide a conclusive assessment of the effect of day hospices on symptom control and quality of life. However, early evidence on the potential benefit of day hospices to palliative care patients exists. Due to the limited transferability of international studies to the German health care system, the heterogeneous implementation of day hospice structures in individual studies and the partly different study quality, a direct transfer of structures, offers, and effects of day hospices, in the German health care system is not possible [1, 8, 9]. However, the positive effects resulting from social interactions [2, 5] have already been demonstrated in Germany as well; specifically the participation in social life is often difficult among palliative patients. The introduction of joint leisure activities (“palliative excursions”) in terms of “Adventure Therapy” led to a temporary strengthening of social interaction and quality of life [10, 11]. There are also first indications for day hospices in Germany, with both patients and their relatives expecting benefits from the introduction of day hospices [12]. Additionally, theoretical recommendations for the establishment and expansion of day hospices in Germany have now been published [8, 13].

Thus far, only a few day hospices exist in German-speaking countries, unlike in Anglo-Saxon countries, where they are already widely established in the medical field [2, 4, 14, 15]. Systematic planning for the establishment of day hospices does not yet exist [8]. The experience and knowledge of the effects and structures of day hospices in Germany under everyday conditions have not been extensively studied [9]. In April 2022, the “Day Hospice Adiuvantes,” which is one of the few independently operated day hospices in Germany, was opened in Vilsbiburg (Lower Bavaria, Germany). The first valid data from real (palliative-) medical and (palliative-) nursing care situations will be obtained in our planned study. Particularly, the structural and interventional framework for the establishment of a day hospice will be systematically and structurally elaborated and tested under daily conditions. For this purpose, the acceptance, adherence, feasibility, and effectiveness of the developed offers will be tested based on reliable data and quality indicators.

## Methods and study design

### Aims of the study

To clarify the fundamental questions of effectiveness, structure, and implementation in real-life practice, a scientific accompanying program is planned during the first 3 years of operation of the “Day hospice Adiuvantes.” Particularly, the following questions will be clarified:

Which structural conditions and interventional measures should be established in the day hospice from the point of view of patients, relatives, and specialist personnel?Are the planned structures or interventions from question 1 feasible under real-life conditions, implementable, and accepted by the affected patients, relatives, and providers?How can, based on the results of questions 1 and 2, a final implementation and intervention catalog for the day hospice be designed?Is the final catalog of services developed under question 3 feasible, reasonable, economical, and effective under everyday conditions in the day hospice?

### Study design

A prospective, three-stage mixed method study (Fig. 1), guided by the Medical Research Council Framework for the Development and Evaluation of Complex Interventions [16] and the MORECare Statement for the Evaluation of Complex Interventions at the End of Life [17], is planned.

**Fig. 1 Fig1:**
[figure not shown]
Study design — flowchart.

#### Stage 1: Method development (Develop/Identify intervention)

Initially, (a) an extensive literature and guideline research (U1) and (b) qualitative individual interviews [18, 19] (U2) on previous offerings and experiences in day hospices will be conducted. The results are the basis for establishing a first theory model (logical model) [20, 21]. This draft model, including a catalog of organization and offerings, will be cross-checked by participants from U2 and day hospice staff and then finalized. The other aspects of Stage 1 represent the precise definition and development of economic data, metrics/instruments, and quality indicators [22], which will be collected for the reviews of interventions and measures in Stages 2 and 3.

#### Stage 2: Feasibility test (Feasibility)

In Stage 2, the feasibility test of the organization and supply catalog created in Stage 1 and the testing of the metrics and quality indicators under real-life conditions will be performed. Survey variables, structures, and interventions can be continuously adjusted in a dynamic process. Finally, the adjusted measures are cross-checked again by participants from U2 (Stage 1) and day hospice staff, and finalized by the authors.

#### Stage 3: Evaluation phase (Evaluation)

Day hospice organization will be adapted to the final catalog of structures and services developed in Stage 2 and, if necessary, new measures will be implemented. These are then to be tested in an 18-month evaluation phase under real-life everyday conditions in a process test [23] for their feasibility, usefulness, effectiveness, and economic efficiency by using the qualitative and quantitative indicators defined in Stage 2.

### Methods

#### Stage 1: Method development (Develop/Identify intervention)

The usual databases (PubMed, Cochrane Library, Google Scholar, and so on) on day hospice, definition, structure, supply, effect, economics, public relations, and quality indicators, among others, will be used in the planned guideline search in U1.

The qualitative individual interviews in U2 will be conducted with experts (palliative physicians, palliative care nurses, primary care providers from day hospices), guests of the day hospice, and their relatives. In joint consultation with the patient, the relative most directly involved in the care should be invited to participate as the primary caregiver. The interview questions will be based on the study objectives and U1 results. The survey will be conducted in cooperation with “SINUS Markt- und Sozialforschung” by trained and experienced personnel via a secure digital communication medium (either audiovisual or audio only). The planned duration per interview is between 30 and 60 min. The interview place and time are coordinated individually with the participants. The exact number of interviews depends on the goal of generating new data (interviews) until no more new topics are obtained [24]. At least 10 individual interviews will be conducted to achieve sufficient data saturation. The interviews are recorded and transcribed for further processing. For the evaluation, the hermeneutic text interpretation according to Oevermann [18] and the qualitative content analysis according to Mayring [19] are used. Qualitative interviews allow open questions and the possibility for the interviewer to clarify ambiguous responses.

To create a structured and comprehensible theory model including a first structure and offer catalog for the further study steps, we will develop a logical model of a day hospice based on U1 and U2 results [20]. For informed and organized decision making in the research group, the nominal group process is used for this purpose [25].

To develop potential quality indicators, sources from the literature [23, 26, 27] and already defined quality indicators of different guidelines, registers, or indicator databases should serve as a basis [1, 28–30]. The quality indicators are then developed in a structured manner analogous to the S3 guideline for quality indicator development [22] (Table 1).

**Table 1 Tab1:** Potential parameters for quality indicators

*Patients*	*Relatives*
Quality of life	Quality of life
Social integration and interaction	Relief for family caregivers inpatient care at home
Physical symptom control	Stress reduction for family caregivers
Psychological symptom control	Perceived quality of care of the day hospice
Perceived quality of care of the day hospice	Duration of feasible home care by family caregivers
Duration of a possible antiproliferative therapy (motivation for therapy)	Financial burden
Overall survival	Satisfaction with the care
Number of hospitalizations	
Cost of health care	
Satisfaction with the care	

Quantitative data collection will be based on structured and validated questionnaires or palliative care assessment tools, which are further supplemented by the authors with medical (ECOG, degree of care, and so on), epidemiological, demographic (marital status, residential and social background, and so on), and health economic data (Tables 1 and 2). The health economic evaluation should focus on cost differences in both groups, structural resources of the health care system used (SAPV, nursing services, hospital admissions, medication consumption, and so on), and quality of life [31–33]. For this purpose, a collaboration with the “Allgemeine Ortskrankenkasse Bayern (AOK)” is planned. Before the final release of the collected quantitative data, the questionnaires will still be subjected to a pre-test [34].

**Table 2 Tab2:** Intended measuring instruments

*Patients*	*Relatives*
EORTC QLQ-C15-PAL [40]	Häusliche Pflege-Skala (HPS-10) [41]
POS – Palliative care Outcome Scale [42] Palliative Care Assessment Questionnaire - Questionnaire for Patients	POS – Palliative care Outcome Scale [42] Palliative Care Assessment Questionnaire - Questionnaire for family caregivers
Disstress Thermometer [43]	Disstress Thermometer [43]
EORTC QLQ-IN-PATSAT32 [44]	EORTC QLQ-IN-PATSAT32 [44]
Minimal documentation system MIDOS to distressing symptoms [45]	QOLLTI-F v2@ - Quality of life during serious illness - family caregivers [46, 47]
Core data set of the national hospice and palliative registry [48]	

#### Stage 2: Feasibility test (Feasibility)

The contents of the (theoretical) offer catalog are established based on the day hospice structures. In a 6-month test phase, the review will then take place:

Quantitatively using the measurement tools, target measures, and quality indicators developed in Stage 1. During the test phase, data quality, practicability, and applicability of the planned measurement instruments and quality indicators will be regularly reviewed in daily clinical practice and adjusted if necessary.Qualitative by means of individual participant interviews (patients, relatives, caring medical staff of the day hospice). The qualitative interviews will be conducted regularly during the test phase and analogously to Stage 1. In principle, at least 10 individual interviews are planned, with the questions focusing primarily on the feasibility, acceptance, and implementation possibilities of the structures and services developed in Stage 1 in daily clinical practice.

Based on the data obtained, at the end of the feasibility test, the authors will adapt and finalize the quantitative survey instruments, quality indicators [22], and logical model [20, 21], including the catalog of organizations and services in a renewed nominal group process [25].

#### Stage 3: Evaluation phase (Evaluation)

The process test will be performed as follows:

Use of the quantitative indicators finally defined in Stage 2: structured questionnaires, quality indicators, and medical, epidemiological, demographic, and health economic data.Conduct an initial, baseline, quantitative effectiveness review on the potential benefits of the day hospice. For this purpose, a cohort study [35] with two comparison groups [A — “patients/relatives in the catchment area of the day hospice” (patients living in the catchment area of the day hospice: radius ≤ 25 km approach distance) vs. B — “patients/relatives outside the catchment area of the day hospice” (patients living outside the catchment area of the day hospice: radius > 25 km travel distance)] is planned [12]. The patients (and their relatives) in group A are also cared for in the day hospice, whereas, those in group B are not cared for in the day hospice, but medical care is provided in the same network structure (oncology–palliative care network Landshut, Lower Bavaria, Germany). The oncology–palliative care network Landshut includes several regional hematology–oncology outpatient clinics, an inpatient palliative medicine–oncology care unit, a SAPV, and an inpatient hospice. The network provides for the catchment area of the investigated day hospice and other regions without day hospice facilities to ensure comparability of the two cohorts based on the same oncology and palliative care structures.Due to the palliative disease situation of the participants with significantly limited life expectancy, quantitative data will be collected at the measurement time points T0 (baseline, after study inclusion), T1 (after 4 weeks), and T2 (after 8 weeks) (Fig. 2).Individual qualitative interviews will be conducted with the patients and their relatives on an ongoing basis during the evaluation phase in the same way as in Stage 1. Approximately 25–35 interviews are planned, with questions focusing on the perceived benefit from day hospice.

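### Three potential duration indicators (survival, home care, antiproliferative therapy) are cut off at 8 weeks because no later quantitative observation is stated

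*Protocol article*

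**What the plan says.** The Methods section on Stage 3 describes a cohort study comparing patients inside and outside the day hospice's catchment area. It states that "quantitative data will be collected at the measurement time points T0 (baseline, after study inclusion), T1 (after 4 weeks), and T2 (after 8 weeks"). The reason given is "Due to the palliative disease situation of the participants with significantly limited life expectancy". The same section counts structured questionnaires, quality indicators, and medical and health economic data among the quantitative indicators, and the schedule sentence exempts none of them. No later contact or record follow-up is mentioned.

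Table 1 (Methods, Stage 1) is headed "Potential parameters for quality indicators". For patients it includes "Overall survival" and "Duration of a possible antiproliferative therapy (motivation for therapy"); for relatives it includes "Duration of feasible home care by family caregivers". It also lists "Number of hospitalizations" and health care costs. The list is provisional: Stage 3 is to make "Use of the quantitative indicators finally defined in Stage 2". For the economic evaluation, a collaboration with a statutory health insurer is planned, with no observation window stated.

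**The concern.** A duration is fully observed only when its end is observed. Survival ends with death, home care with permanent institutional admission or death, and therapy with its last administration or death. A patient who is alive, at home and on treatment at week 8 contributes only the information that each duration exceeded 8 weeks.

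The reason given for the short schedule suits questionnaires, which burden very ill people and soon go missing. It does not carry over to dates that can be read from records. If life expectancy is short, following such dates to completion is easier, not harder.

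What is at stake is limited but real. The Background names the support of care at home as one purpose of day hospices, and home-care duration is the listed indicator closest to it. If it is retained and cut at 8 weeks, any difference that emerges later cannot be seen. The collection window and the scope of consent must also be settled before Stage 3, because dates that were never collected cannot be recovered at analysis.

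**Working it through.** **Is there a figure to reproduce?** No. The section on expected sample size bases 80 patients per group on feasibility and caseload, without effect size, event rate or power. The check is therefore how much of a duration an 8-week window observes.

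**Inputs from the protocol article**
- Last quantitative time point: 8 weeks (Methods, Stage 3).
- Recruitment: 18 months, taken as 78 weeks (Expected sample size).
- Patients: 2 × 80 = 160 (Expected sample size).
- Two-sided significance level: 0.05 (Statistical analysis).

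**Assumptions, not in the documents**
- Exponential durations with median *m* weeks, so λ = ln 2 / *m*.
- Uniform entry over the 78 weeks.
- Alternative follow-up to the last patient's T2, at 78 + 8 = 86 weeks, so that individual follow-up is uniform between 8 and 86 weeks.

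**Formulas**
- Censored at 8 weeks: exp(−8λ) = 2^(−8/m).
- Censored at the common cut-off: [exp(−8λ) − exp(−86λ)] / (78λ).
- Events: 160 × (1 − censored share).

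**Example, m = 26 weeks.** λ = 0.02666. At 8 weeks: exp(−0.2133) = 0.808, giving 160 × 0.192 ≈ 31 events. At the common cut-off: (0.808 − 0.101) / 2.079 = 0.340, giving 160 × 0.660 ≈ 106 events.

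| Assumed median (weeks) | Censored at 8 weeks | Events | Censored at last patient's T2 | Events |
|---|---|---|---|---|
| 4 | 25% | 120 | 2% | 157 |
| 6 | 40% | 97 | 4% | 153 |
| 8 | 50% | 80 | 7% | 148 |
| 12 | 63% | 59 | 14% | 138 |
| 26 | 81% | 31 | 34% | 106 |
| 52 | 90% | 16 | 56% | 71 |

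The censored share exceeds one half only when the median is above 8 weeks. Longer follow-up observes more events at every median tried.

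**Would longer follow-up make the comparison adequately powered?** By Schoenfeld's formula with equal groups, 80% power needs 4 × (1.96 + 0.842)² / (ln HR)² events. An assumed hazard ratio of 0.7 needs 247, more than the 160 patients planned. At medians of 8, 12, 26 and 52 weeks, power for 0.7 is 36%, 28%, 17% and 11% with the 8-week cut, and 58%, 55%, 45% and 32% with the longer follow-up. A hazard ratio of 0.5 needs 66 events, which the longer follow-up reaches at all four medians and the 8-week cut reaches only at 8 weeks.

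**Hospitalisations and costs.** These are a count and a sum. Over a common 8-week window they are complete apart from death and dropout, so the calculation above does not apply to them.

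**The case against.** The case for leaving the plan as it is has four parts.

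*The indicators are provisional.* Table 1 lists candidates, and the three durations may be dropped or redefined after Stage 2. This stands, and it makes the point conditional on their being retained.

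*Record-based data may follow another timetable.* Fig. 2 is not shown, its caption separates questionnaires from structural and economic data, the evaluation phase lasts 18 months, and the insurer data have no stated window. This stands for the insurer data. For the rest, the available text leans the other way: the schedule sentence covers quantitative data without exception, and the Fig. 2 caption calls only the interviews continuous.

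*An article condenses the full protocol, and censoring rules belong in the analysis plan.* The method of analysis can indeed be left there and is not criticised here. The point rests on the stated schedule, which does not fit the listed durations.

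*Survival may be short.* The admission criteria require very advanced or terminal disease. With a median of 4 weeks only 25% would be censored, so heavy censoring cannot be asserted as fact.

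A reader might go further and infer that the effectiveness and economic parts of question 4 will rest mainly on censored durations. The documents do not support that. Most parameters in Table 1 and nearly all instruments in Table 2 are questionnaire constructs that fit 0, 4 and 8 weeks, and hospitalisations and costs are not durations. A reader might also infer that a null result would be produced by the window alone. That does not follow either: at a median of 12 weeks about 59 deaths would fall within 8 weeks, so a large difference could show, and 160 patients are too few for a moderate one at any follow-up length.

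**Conclusion.** The point holds for three potential indicators: overall survival, duration of feasible home care and duration of antiproliferative therapy. As written, the schedule cuts them off at 8 weeks, and the reason given for it does not apply to dates held in records. At assumed medians of 8 to 52 weeks, 50% to 90% would be censored, against about 7% to 56% with follow-up to the last patient's T2. These figures rest on exponential durations, uniform entry over 18 months and medians that the documents do not supply.

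The point is modest in weight. The study is exploratory, the indicators are not yet final, and the questionnaire outcomes are unaffected. Correcting the window would make the description of these durations more complete; it would not give adequate power for a moderate effect such as a hazard ratio of 0.7.

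**What to change.** 1. Keep the questionnaires at T0, T1 and T2.
2. For each of the three durations retained after Stage 2, state that dates are taken from network records in both cohorts until death or one common cut-off, namely the last patient's T2. Analyse them from T0 as time-to-event outcomes, with the ending event defined (for home care, permanent institutional admission or death).
3. If longer follow-up is not wanted, rename the indicator as a status at 8 weeks.
4. Report hospitalisations and costs over one stated window common to both cohorts, or as rates per time at risk, and state the window of the insurer data.

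The cost is a sentence or two in the protocol, consent wording for record-based follow-up, and one record look-up per patient at database closure, with no extra visits or questionnaires. A record source must also be named for the control cohort, since the section on data collection names the digital patient file only for day hospice guests. The natural moment is the finalisation of indicators at the end of Stage 2, before the cohort opens.
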